## Abstract

**Background:**

Childhood obesity is a growing concern for public health. Given a majority of children in many countries spend approximately 30 h per week in early childcare centers, this environment represents a promising setting for implementing strategies to foster healthy behaviours for preventing and controlling childhood obesity. Healthy Start-Départ Santé was designed to promote physical activity, physical literacy, and healthy eating among preschoolers. The objectives of this study are to assess the effectiveness of the Healthy Start-Départ Santé intervention in improving physical activity levels, physical literacy, and healthy eating among preschoolers attending early childcare centers.

**Methods/Design:**

This study follows a cluster randomized controlled trial design in which the childcare centers are randomly assigned to receive the intervention or serve as usual care controls. The Healthy Start-Départ Santé intervention is comprised of interlinked components aiming to enable families and educators to integrate physical activity and healthy eating in the daily lives of young children by influencing factors at the intrapersonal, interpersonal, organizational, community, physical environment and policy levels. The intervention period, spanning 6-8 months, is preceded and followed by data collections. Participants are recruited from 61 childcare centers in two Canadian provinces, New Brunswick and Saskatchewan. Centers eligible for this study have to prepare and provide meals for lunch and have at least 20 children between the ages of 3 and 5. Centers are excluded if they have previously received a physical activity or nutrition promoting intervention. Eligible centers are stratified by province, geographical location (urban or rural) and language (English or French), then recruited and randomized using a one to one protocol for each stratum. Data collection is ongoing. The primary study outcomes are assessed using accelerometers (physical activity levels), the Test of Gross Motor Development-II (physical literacy), and digital photography-assisted weighted plate waste (food intake).

**Discussion:**

The multifaceted approach of Healthy Start-Départ Santé positions it well to improve the physical literacy and both dietary and physical activity behaviors of children attending early childcare centers. The results of this study will be of relevance given the overwhelming prevalence of overweight and obesity in children worldwide.

**Trial registration:**

NCT02375490 (ClinicalTrials.gov registry).

## Background

Childhood obesity is one of the greatest challenges facing public health in the 21^st^ century [1–3]. Weight in early childhood closely predicts weight in later childhood [4–6] and children under six who are obese are at four times more at risk of becoming obese adults than normal weight children [7, 8]. Further, being overweight during childhood increases the likelihood to have compromised emotional, psychological and social well-being [9].

Many factors come together to produce obesity, but it is primarily due to an imbalance between energy intake and energy expenditure [10]. Eating habits are established early in childhood and usually persist for many years [11]. Data show that only 29 % of Canadian preschool aged children meet recommendations for fruit and vegetable intake and 23 % for grain products [12]. Further, 79 % of 4-5 year olds consume food of little nutritional value (e.g., chips, french fries, candy, chocolate, soft drinks, cake and cookies) at least once a week [12] and other studies have demonstrated that empty calories are making up as much as 40 % of their total caloric intake [13, 14]. Similarly, a recent review found that children in early childcare centers (ECC) have low levels of physical activity, and that they are sedentary for much of the time [15]. It was estimated that children in childcare settings accumulate an average of only 7 to 13 min of moderate to vigorous physical activity during the course of a 7 h day [16]. Moreover, recent data show that many of them have poor physical literacy [17–21]. These data are troubling given that sedentary state and physical activity levels track over time [22–26].

Interventions designed to improve the physical activity and nutrition of preschoolers are needed to prevent and control childhood obesity [1, 27–29]. Since more than half of Canadian preschoolers spend an average of 29 h a week in ECC [30], this environment is a prime setting for implementing an array of strategies to foster healthy behaviours [31–36]. However, two systematic reviews on obesity prevention in children under 5 years, one on interventions [35] the other on preventive policies, practice and interventions in ECC [36], reported limited success in improving physical activity levels, dietary behaviour, or body composition. The authors suggest that the least successful interventions focused only on one or two outcomes, while the most successful interventions positively influenced factors such as knowledge, abilities and competence. According to the authors, this means that interventions should be grounded in comprehensive behaviour change models, be multifaceted and sustained over time [35]. Few interventions focused on physical activity and eating behaviours simultaneously, therefore future interventions should target both behaviours [36]. It can be concluded that interventions promoting healthy weights in children should encompass a broad spectrum of concerted actions and be based on best available knowledge from research and practice [16, 37].

Healthy Start-Départ Santé, a multilevel intervention that targets physical activity, physical literacy, and healthy eating in preschoolers, was developed following these principles. The aim of the current study is to lead a comprehensive evaluation of the Healthy Start-Départ Santé intervention using an experimental research design.

### The intervention

Healthy Start-Départ Santé uses a population health approach to promoting physical activity and healthy eating among English- and French-speaking preschoolers between 3–5 years old who attend ECCs (e.g., licenced childcares or preschools). The population health approach posits that to positively influence population-level health outcomes, interventions must take into account the wide range of health determinants [38], recognise the importance and complexity of potential interplay among these determinants, and reduce social and material inequities [39]. Further, they must rely on best evidence available, stimulate intersectoral collaborations, and provide opportunities for all potential stakeholders to be meaningfully engaged from the onset to their deployment [39]. Several models based on the population health approach have been developed to steer interventions [40–42] and, similar to ecological models [43], they call for interventions to include a series of concerted actions capable of targeting all levels of influence such as the intrapersonal (biological and psychological), interpersonal (social and cultural), organizational, community, physical environment and political levels. Healthy Start-Départ Santé includes strategies for each level of influence. Supported by local funding, and then by Phase I of the Public Health Agency of Canada Innovation Strategy (2008-2012), Healthy Start-Départ Santé was developed by researchers, community groups, educators, parents, and government representatives, pilot tested, and adapted to diverse contexts. In particular, Healthy Start-Départ Santé was linguistically and culturally adapted to cater to both official linguistic groups in Canada, which is important since it has been documented that to be effective, interventions must be tailored and implemented using several different socio-linguistic perspectives as befitting the target population [44].

The mission of Healthy Start-Départ Santé is to encourage and enable families and educators to integrate physical activity and healthy eating in the daily lives of young children. Specifically, Healthy Start-Départ Santé attempts to influence factors at the intrapersonal (e.g., eating and physical activity behaviour of children), interpersonal (e.g., educators and parents), organizational (e.g., ECC), community (e.g., community organization involvement), physical environment and political levels (e.g., built environment and policies). The intervention is composed of six interlinked components which are presented in more detail in Fig. 1. These components include: 1) intersectoral partnerships conducive to participatory action that leads to promoting healthy weights in communities and ECC; 2) the Healthy Start-Départ Santé implementation manual for educators on how to integrate healthy eating and physical activity in their centre; 3) customized training, role modelling and monitoring of Healthy Start-Départ Santé in ECC; 4) the evidence-based resource, LEAP-GRANDIR [16], which contains material for both families and educators; 5) supplementary resources from governmental partners; and 6) a knowledge development and exchange (KDE), and communication strategy involving social media and web-resources to raise awareness and mobilize grassroots organizations and communities. Healthy Start-Départ Santé is delivered over 6-8 months and includes a partnership agreement, an initial training session which orients ECC staff to the concepts, the implementation manual and the use of resources, on-going support and monitoring over time, one tailored booster session, and a family day to celebrate the ECC’ success at the end of the intervention.

**Fig. 1 Fig1:**
[figure not shown]
Healthy Start components

### Study objectives

It is hypothesized that, in comparison to usual practice, exposure to the Healthy Start-Départ Santé intervention will lead to improved opportunities for physical activity and healthy eating hence to increased physical activity and healthier eating among children. The specific study objectives are to assess whether:The Healthy Start-Départ Santé intervention leads to increases in opportunities for physical activity and healthy eating in ECC through improved knowledge, attitudes and self-efficacy of the educators and directors;The Healthy Start-Départ Santé intervention leads to increases in physical activity levels and healthy eating behaviors among preschoolers, in turn promoting healthy weights;The Healthy Start-Départ Santé intervention leads to improvements in physical literacy among preschoolers.

## Methods/Design

### Study design

The Healthy Start-Départ Santé evaluation follows a delayed cluster randomized controlled trial design in which the ECCs are randomly assigned to receive the intervention or serve as usual practice controls. The intervention spans a period of 6–8 months. This period is both preceded and followed by data collections (Fig. 2). Control sites are given the option of receiving the intervention once their participation in the evaluation has been completed. Data collection takes place over three years, such that approximately a third of ECCs recruited will complete the study each year. This study protocol received ethics approval from Health Canada, the University of Saskatchewan, and the Université de Sherbrooke.

**Fig. 2 Fig2:**
[figure not shown]
Data collection timeline for the Healthy Start study

### Target population and sampling

Participants for the Healthy Start-Départ Santé project are recruited from 61 French and English ECCs in two Canadian provinces: New Brunswick and Saskatchewan. Province-specific recruitment and data collection are carried through a study coordinating center established in each province. Both coordinating centers follow the same protocols. Specifically, a registry of all licenced ECCs in both provinces is obtained. From this list we exclude any ECC which has already received a physical activity or nutrition promoting intervention in the past. This avoids underestimating the effect of the Healthy Start-Départ Santé intervention. To be included in the study, an ECC has to prepare and provide meals for lunch. This is required for assessing the quality of foods being served and for measuring nutritional intake. For feasibility and efficiency reasons, the number of children attending the ECC also serves as an exclusion criterion; centers with less than 20 children between the ages of 3 and 5 are not considered. Information on these criteria is obtained from governmental partners or through a brief telephone administered questionnaire. In order to obtain a final sample of at least 735 children, we estimated that a minimum of 15 children aged 3 to 5 would need to be recruited in 62 ECCs. A minimum of 20 children per center was established to account for a 60 % participation rate (Recruiting 60 % of eligible children in 62 ECCs would give a total of approximately 744 participants). Despite planned measures to minimize losses to follow-up, this issue is inevitable in a longitudinal study of this nature. Based on pilot work, we anticipate an attrition rate of approximately 5 %, which will provide adequate statistical power to conduct the planned analyses. The target of 735 children was based on estimates that 700 (735 - 5 %) participants divided into two groups of 350 participants will provide 80 % power to detect a 10 % between-group difference in outcome considering a within-group standard deviation of 40 %, α = 0.05, intra-class correlation of 0.02, and collinearity between the intervention and other explanatory variables expressed by an estimated multiple correlation of 0.15.

For recruiting purposes, the ECCs are stratified according to province, geographical location (urban and rural) [45] and their respective school district (English or French) (Fig. 3). This stratification process ensures relatively homogenous strata for comparisons, since curriculum can differ between ECCs under different district authorities and that the ECC environment can be influenced by its geographical location [46, 47]. Once stratification is completed, eligible ECCs are randomly selected through a sequence generated using Stata SE statistical software (StataCorp, College Station, TX) according to the above-mentioned strata. Given the large area Saskatchewan represents (652 000 km^2^), it was decided to carry the study with selected ECCs in the central region in year 1, and in the South and central-North in years 2 and 3. Selected ECC are contacted, provided with information, and invited to participate in the project. Subsequently, ECC directors are telephoned to answer their questions and to confirm their participation while securing the parents’ board support. The recruited ECC are then sent consent forms. Centres which decline participation or with fewer than five children recruited are replaced by other randomly selected ECC from the same stratum. Once the ECC provides final consent, it is randomly allocated to the intervention or usual practice (control) arm. A one to one randomization protocol is applied to each stratum. Invitation packages describing the study and seeking parental consent are sent to parents of all age-eligible children. ECCs return completed parental consent forms to the provincial coordinating centres. Following recruitment of one ECC and its children in the usual practice arm, it was found that it had the same director and shared staff with a nearby ECC that had been recruited in the intervention arm. Given the risk for contamination was regarded as being certain in this situation, the two ECC are considered as one intervention arm ECC, which explains the final sample of 61 ECC enrolled in the study.

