### Data analysis

As a first step, each variable distribution will be examined in order to manage obvious errors such as outliers or questionable input. If necessary, appropriate transformations will be applied. If there are systematic missing variables, these will be filled using multiple imputation methods. After the initial data cleaning and processing, descriptive analyses will be used to characterise the two groups of participants and their context.

Analyses of the main study objectives will adhere to the intention-to-treat principle. Multiple linear regression will be used to determine if, in comparison to participants in the usual care group, participants exposed to Healthy Start-Départ Santé had greater increases in ECC-provided opportunities for physical activity, ECC-provided opportunities for healthy eating, in physical activity levels, in healthy eating behaviours, and if they had greater improvements in physical literacy. A multilevel approach will be used in each model to account for clustering that could result from children attending the same ECC. Potentially confounding variables (i.e., age, parental education, household income, etc.) will be included in the models.

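### On the stated order of steps, centres are randomised before parents are invited, so which children join, and possibly which centres stay, can depend on the arm

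*Protocol article*

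**What the plan says.** All the steps stand in one paragraph of the Protocol article, under Target population and sampling, in this order:

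1. Centres are selected at random, contacted and sent consent forms.
2. Replacement: "Centres which decline participation or with fewer than five children recruited are replaced by other randomly selected ECC from the same stratum".
3. Allocation: "Once the ECC provides final consent, it is randomly allocated to the intervention or usual practice (control) arm". The ratio is fixed by stratum: "A one to one randomization protocol is applied to each stratum".
4. Parents: "Invitation packages describing the study and seeking parental consent are sent to parents of all age-eligible children".
5. Forms: "ECCs return completed parental consent forms to the provincial coordinating centres".

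The paragraph then reports a problem found at one site: "Following recruitment of one ECC and its children in the usual practice arm, it was found that it had the same director and shared staff". The other site concerned was a neighbouring intervention centre.

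The sample-size paragraph of the same section gives the expected uptake: "A minimum of 20 children per center was established to account for a 60 % participation rate". Data analysis adds: "Analyses of the main study objectives will adhere to the intention-to-treat principle". The article describes no masking of centre staff, parents or recruiters, and does not say when a centre learns its arm.

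**The concern.** In a cluster trial, randomising centres makes the centres comparable. It makes the children comparable only if they are identified and consented without regard to the arm. Here the invitation follows allocation, and the centre that handles the forms may already know whether it will receive the programme. If about four families in ten stay out, the families who join an intervention centre may differ from those who join a control centre, for example in their interest in activity and food. The named covariates (age, parental education, household income) do not measure that interest.

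The replacement rule could add a second route. If it operates after allocation, it drops whole randomised centres on a count that the arm can influence. That is a post-randomisation exclusion, which intention to treat does not allow. The text also does not say whether a substitute centre takes over the dropped centre's arm or is randomised afresh.

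**Working it through.** **Order of steps.** The count of recruited children (step 2) needs parental consent (steps 4 and 5). Allocation (step 3) is tied to the centre's consent, not the parents'. Two readings are possible:

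- *Parents are invited after allocation, as the sentences run.* The five-child count then exists only after allocation, so replacement for low recruitment removes a randomised centre, although its sentence stands before the allocation sentence.
- *Children are counted before allocation.* The replacement rule is then harmless, but the invitation sentence is in the wrong place.

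The paragraph cannot be right in both respects.

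**The plan's own figures.** Expected recruitment is 62 × 20 × 0.60 = 744, as stated. The target difference is 10/40 = 0.25 SD. The base size is 2 × (40 × (1.96 + 0.8416)/10)² = 251.2 per arm (two-sided α assumed). With ICC 0.02 and 20 children per centre, the design effect is 1 + 19 × 0.02 = 1.38, which gives 346.6. The factor 1/(1 − 0.15²) = 1.023 gives 354.6. The stated 350 per arm is reproduced to within 3 %. The article does not state the cluster size used. None of these figures is in dispute.

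**How large selection could be (assumed inputs).** With consent rate p and a gap g between consenters and refusers, the mean of consenters is the population mean + (1 − p) × g.

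- Consent 60 % in both arms, with g larger by 0.25 SD in one arm: 0.40 × 0.25 = 0.10 SD, or 0.10/0.25 = 40 % of the target.
- Consent 65 % v 55 %, with g = 0.5 SD in both: (0.45 − 0.35) × 0.5 = 0.05 SD, or 20 % of the target.

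On the plan's scale (SD 40) these are 4 and 2 points. With 20 × 0.60 = 12 children per centre, the design effect is 1.22 and SE = 40 × √(2 × 1.22 × 1.023/350) = 3.38 points. The two-sided error rate with a bias b is Φ(−1.96 + b/SE) + Φ(−1.96 − b/SE):

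| Bias surviving into the analysed quantity | Type I error |
|---|---|
| 0 | 0.05 |
| 2 points | 0.09 |
| 4 points | 0.22 |

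**What the planned comparison removes.** Main outcome measures has each measure taken before and after in both arms, and Data analysis compares increases and improvements. A level difference that is the same at both times cancels in a change. Only selection related to change survives in full, so the table is an upper illustration for selection on level.

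**How often the five-child rule would fire.** For a centre with 20 eligible children, the stated minimum, P(fewer than 5 recruited) under a binomial model is:

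| Participation | Probability per centre |
|---|---|
| 60 % | 0.0003 |
| 40 % | 0.05 |
| 30 % | 0.24 |
| 25 % | 0.41 |

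At 60 % this is 62 × 0.000317 = 0.02 centres expected in all. If participation varies between centres (beta-binomial, assumed intra-centre correlation 0.1 to 0.2), the probability is 0.026 to 0.077, or 62 × 0.026 = 1.6 to 62 × 0.077 = 4.8 centres. Larger centres would trigger the rule less often. The rule matters mainly if one arm recruits far below plan.

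**The case against.** The best defence has five parts.

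- **Replacement is not dated.** Its sentence precedes the allocation sentence, and the invitation sentence carries no time word. A reader might infer that randomised centres were in fact dropped. The text does not show that, and the flow diagram (Fig. 3), which might settle it, is not available here. This part stands, and the intention-to-treat conflict is therefore conditional on the order given.
- **The shared-director account is weak evidence of timing.** It speaks of children recruited in the usual practice arm, but it also calls the neighbouring centre recruited in the intervention arm, although centres are recruited before allocation. The arm may be a label applied afterwards. This stands; the account fits the stated order but does not prove it.
- **Staff may not yet know the arm.** The time of disclosure is not given, invitations go to all age-eligible families, and control centres are offered the programme later (Study design), which may narrow any difference in motivation. These points lessen the risk. They do not remove it, because nothing described keeps the arm from those who handle recruitment.
- **The illustrations are on outcome level.** A reader might take 40 % of the target as an estimate for this trial. It is not one: the gaps and consent rates are assumed, and the before-after comparison removes stable differences.
- **Re-ordering may come too late.** The article already reports 61 centres enrolled. That limits the first part of the remedy but not the analysis and reporting part.

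**Conclusion.** The point holds in a limited form. On the order the article gives, allocation precedes parental invitation, centres return the forms, and no masking is described, so recruitment of children can depend on the arm. This is a stated design choice, not a detail left to another document. On that same order the five-child rule would exclude randomised centres, in conflict with intention to treat. If replacement really came before allocation, the description of the steps contradicts itself and must be corrected.

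The documents do not show that bias occurred, and its size cannot be estimated from them. The 0.05 to 0.10 SD range rests on assumed consent rates and gaps and applies to outcome level. Differential recruitment of children is the larger risk; at 60 % participation the replacement rule should seldom act.

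**What to change.** **Centres not yet allocated, if any.** Collect parental consent first, ideally also the baseline measures; apply the five-child rule; then randomise. Allow no replacement after allocation.

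**Centres already allocated.** Keep in the intention-to-treat analysis, in its allocated arm, every centre with at least one consented child and data. Adjust for the baseline value of the outcome. Report by arm the numbers of families invited and consented and of centres replaced, and say whether each replacement came before or after allocation.

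**Text.** Rewrite the paragraph so that parental consent, the five-child count, replacement and allocation stand in the order in which they happened.

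**Cost.** The first part re-orders existing steps, leaves slightly less lead time to arrange training, and may reach few or no centres. The second keeps a few very small centres in the analysis and needs counts from the recruitment records. Baseline is already measured in both arms.
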